#### Online assessment

Beyond the screening questions and the assessment of the above mentioned smoking related variables, which will be assessed in both study groups, participants of the intervention group will additionally receive online questions assessing (1) outcome expectancies of smoking cessation, (2) situations in which craving for cigarettes occur, (3) alternative strategies to handle these craving situations, and (4) costs per pack of cigarettes.

#### Weekly SMS assessment

During the 3-month intervention period, participants of the intervention group will receive one text message per week for the assessment of smoking related target behaviour. This question can easily be answered by typing a single letter or number, and using the reply function of the mobile phone. The weekly SMS assessment will be sent at a fixed point in time each week (6 p.m. at the weekday of registration for the program). The content of the question will depend on the HAPA stage as well as on the number of the intervention week.

For all participants, the HAPA stage will be assessed in even weeks by the question: "Have you recently smoked cigarettes?" with the following response options (1) "Yes, and I do not intend to quit" (preintentional stage), (2) "Yes, but I am considering to quit" (preintentional stage), (3) "Yes, but I seriously intend to quit" (intentional stage), or (4) "No, I quit smoking" (action stage). This question assesses both smoking status and intention to quit over time and the responses to this question allow tailoring the SMS feedbacks according to the current HAPA stage [22].

In odd weeks, we will assess the number of cigarettes smoked per day or week (depending on smoking status: daily/occasionally) in smokers of the preintentional stage; and, we will assess whether smokers in the intention or action stage applied the individually chosen strategies to cope with craving situations (e.g. "Did you apply the following strategy recently? When I am on a party, I distract myself from smoking by dancing.").

#### Individually tailored text messages

On the first level, the text messages are tailored to the HAPA stage (preintentional, intentional, action), defined by current smoking status and intention to quit smoking. Persons in the preintentional stage will receive text messages addressing (1) risks of smoking, (2) monetary costs of smoking, (3) social norms of smoking, (4) outcome expectancies, and (5) motivation to reduce the number of cigarettes smoked per day (daily smokers) or week (occasional smokers). Persons in the intentional stage will receive text messages which (1) motivate to use social support for smoking cessation, (2) provide strategies to cope with craving situations, and (3) provide tips for preparing smoking cessation (e.g., reducing the number of cigarettes, identifying craving situations). Persons in the action phase will receive text messages (1) motivating to reward themselves for staying abstinent, (2) providing strategies to cope with craving situations, and (3) motivating to use social support for staying abstinent.

On the second level, the text messages are tailored according to the individual information provided at the baseline assessment as well as through the weekly SMS assessments. Exemplary text messages are displayed in Table 1.

**Table 1 T1:** Exemplary text messages

HAPA stage	Content category	Exemplary text message
Preintentional Stage	Social Norms	Hey Mika. Did you know, not smoking is in! A survey from the University of Zurich found that among 16-to-17-year old female adolescents, only 11% still smoke cigarettes daily.
	
	Outcome Expectancies	Hello Mika. You have the opinion, that after having stopped smoking you will be able to breathe deeply more easily again. That's totally correct! Already after the first weeks you are going to notice strong changes: you will be able to breathe more freely, will be fitter at sports and you will be less susceptible to diseases.
	
	Monetary costs of smoking	You smoke approximately 8 cigarettes less in comparison to the beginning of the program SMS-COACH. Thus, you save approximately 70 Swiss francs per month.

Intentional Stage	Social support for smoking cessation	There are forums online in which smokers and ex-smokers exchange their experiences on smoking cessation. Have a look at www.stop-tabac.ch
	
	Preparing smoking cessation	Hi Peter. Maybe you can avoid smoking cigarettes in situations in which you usually smoke by keeping yourself busy. For example, when having a break or waiting for the bus it can be extremely helpful to have a chewing gum or write an SMS.

Action Stage	Reward for staying abstinent	You can be proud of yourself to not smoke anymore. Reward yourself by buying something that you have desired for a long time.

	Coping with craving situations	Great job, Vince: journals or a book can help you to bridge time when waiting. If there is a moment in which you have nothing readily to hand, you can also distract yourself by using your cell phone for calling somebody or sending a text message to someone.

#### Integrated program for quit day preparation and relapse prevention

Persons in the intentional and action stage will have the possibility to additionally participate in an integrated program for quit day preparation and relapse prevention. Program participants in these phases will be informed biweekly about this option. After entering a scheduled quit day (e.g. "08.12.2011") this program will provide up to two daily text messages (weeks -1 to +1: two daily SMS; weeks +2 and +3: one daily text message) in order to prepare for the quit day and to prevent a subsequent relapse. For example, at the evening prior to the scheduled quit day, participants will receive the following text message: "SMS-COACH EXTRA: Good evening Jona. Tomorrow is your first smoke-free day. Throw away all cigarettes, ashtrays, and lighters tonight. Buy some peppermint sweets or chewing gums for tomorrow."

Study participants of the assessment only control group will not receive any of the above described intervention elements of the SMS-COACH.

### Outcomes

Computer assisted telephone interviews will be conducted at the six months follow-up assessment by trained interviewers. The primary outcome measure will be *7-day point prevalence smoking abstinence*, i.e. not having smoked a puff within the past seven days preceding the follow-up [23].

Secondary outcome measures will include *30-day point prevalence smoking abstinence, self-efficacy for smoking cessation *(action self-efficacy according to the HAPA-model [17]), *nicotine dependence *assessed by the *Heaviness of Smoking Index *(using self-reported time to the first cigarette of the day and number of cigarettes smoked per day [24]), and *quit attempts *within the past six months preceding the follow-up.

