### Participant recruitment and baseline assessment

Smoking apprentices will be recruited at vocational schools in Switzerland. Contact teachers for addiction prevention in approximately 30 Swiss vocational schools will be invited to participate with some of their classes in a study testing the efficacy of a text messaging based smoking cessation program. Participating contact teachers will schedule one school hour per school class for the screening of eligibility criteria, study information, and baseline assessment. Study participants will be recruited by study assistants (graduate students of psychology). The study assistants will invite all apprentices from a school class to participate in an online health survey during a regular school lesson, reserved for health education. Furthermore, they will inform the apprentices that some persons will be invited to participate in a study testing the efficacy of a text messaging intervention for health promotion. To decrease reporting bias the study assistants will not provide more information about the purpose of the study before the screening of eligibility criteria will be completed. Afterwards the apprentices will be invited to fill in an online screening. The screening includes the assessment of demographic data, alcohol consumption, weekly physical activity, smoking status, and ownership of a mobile phone. Inclusion criteria for study participation are (1) daily or occasional cigarette smoking (at least 4 cigarettes in the preceding month and at least one cigarette during the preceding week) and (2) ownership of a mobile phone. Subsequently, eligible persons will be informed about the aim of the study, the intervention arms, assessments, reimbursement, and data protection. Study information will be provided online and in paper form by the study assistants. Reimbursement of 10 Swiss francs (~ € 8.00) for participation at the follow-up assessment after 6 months will be offered to all study participants. Reimbursement of 1 Swiss franc (~ € 0.80) will be offered to the participants of the intervention group for each SMS response to the weekly SMS assessments within the program. After receiving informed consent online, all study participants will be invited to choose a username and to provide their mobile phone number. Furthermore, the following smoking related variables will be assessed: intention to quit, daily/weekly cigarette consumption, time to first cigarette in the morning, past quit attempts, smoking status of friends and parents, and age of smoking onset.

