### Sample size calculation

Based on results of a similar study which tested the efficacy of proactive telephone counselling for smoking cessation in high school students [19], we expect an 8% difference in 7-day point prevalence abstinence rates between the intervention and the control condition at 6-months follow up assessment (25% versus 17%, respectively). A sample size of n = 406 in each study group would have 80% power for a Chi-Square Test (*α *= 5%, 2-sided) in order to detect this difference based on a calculation using *G-Power*. As apprentices are nested within school classes, we additionally needed to consider a potential design effect of 1.12 (assumed class size: 20 apprentices; 35% study participants resulting in an average cluster size of n = 7; intra-cluster correlation coefficient: 0.02) resulting in a required sample size of n = 455 per study group and a total of N = 910 study participants.

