### Data analyses

We will use regression models to test the efficacy of the intervention on the different outcome measures. If necessary, we will control for baseline differences by adding additional baseline variables as covariates to the regression models. All analyses will be performed considering the intention-to-treat principle. Given the clustered nature of the data (apprentices within school classes) we will compute robust variance estimators for all regression analyses.

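### The nicotine-dependence index uses two per-day items in a sample that includes occasional smokers, so it has little room to show a reduction in them, and an unadjusted comparison is likely to lose precision

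*Protocol article*

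**What the plan says.** All references are to the protocol article.

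- **Outcomes.** Nicotine dependence is a secondary outcome at the six-month telephone interview. It is measured by the Heaviness of Smoking Index, "using self-reported time to the first cigarette of the day and number of cigarettes smoked per day". The section does not limit the index to daily smokers. The other secondary outcomes are 30-day abstinence, self-efficacy and quit attempts.
- **Participant recruitment and baseline assessment.** The smoking criterion is "daily or occasional cigarette smoking (at least 4 cigarettes in the preceding month and at least one cigarette during the preceding week". The smoking items asked of both arms at baseline include "intention to quit, daily/weekly cigarette consumption, time to first cigarette in the morning".
- **Weekly SMS assessment.** For intervention participants not yet intending to quit, the odd-week question records "number of cigarettes smoked per day or week (depending on smoking status: daily/occasionally".
- **Individually tailored text messages.** The same group is coached to cut the "number of cigarettes smoked per day (daily smokers) or week (occasional smokers".
- **Data analyses.** Regression models are planned for the different outcomes, with standard errors robust to clustering by class. Baseline covariates enter only where baseline differences make them necessary. "All analyses will be performed considering the intention-to-treat principle".

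**The concern.** Wherever the article records or coaches consumption, it uses a weekly unit for occasional smokers. Only the dependence outcome returns to per-day items for everyone. Someone who smokes a few cigarettes a week has a very small daily count and, on many days, no first cigarette to time. A fall in weekly smoking, which the programme explicitly encourages in this group, can then move the index only slightly.

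Two things are at stake. First, no other listed outcome measures consumption, so the coached reduction in occasional smokers has no outcome suited to detect it. Second, if occasional smokers cluster at the low end of the index, the sample is a mixture of two groups with different means. Without adjustment, the difference between those means enters the residual variance and weakens the comparison of arms. A null result on nicotine dependence could then partly reflect the instrument and the model.

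**Working it through.** **1. The plan's own figure.** The article's only sample-size calculation is for the primary outcome, "25% versus 17%, respectively". With two-sided α = 0.05, 80% power and no continuity correction:

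n = [1.96·√(2·0.21·0.79) + 0.842·√(0.25·0.75 + 0.17·0.83)]² / 0.08² ≈ 406 per arm.

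Design effect = 1 + (7 − 1)·0.02 = 1.12; 406 × 1.12 = 454.72, rounded up to 455 per arm, 910 in total. This reproduces exactly, and nothing below changes it. The article gives no figure for the index.

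**2. Where eligible occasional smokers sit on a per-day scale.** At the eligibility minimum, 4/30 = 0.13 cigarettes per day by the monthly criterion and 1/7 = 0.14 by the weekly one. As an illustration above the minimum, a fall from 10 to 3 cigarettes a week is a 70% reduction, but per day it is only 10/7 = 1.43 to 3/7 = 0.43. Dividing by 7 makes the index computable; it does not give it finer resolution.

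**3. Effect on an unadjusted comparison.** The documents give none of these inputs, so all are assumptions: a share f of occasional smokers fixed at the bottom score (0), and daily smokers with mean m, SD s and arm difference d.

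- Mean arm difference in all participants: (1 − f)·d
- Variance in all participants: (1 − f)·s² + f(1 − f)·m²
- z in all participants divided by z in baseline daily smokers only: s/√(s² + f·m²)

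The ratio is below 1 whenever f and m are above 0, so within this model the direction does not depend on the values chosen. Power follows from z = 1.96 + 0.842 = 2.80 in daily smokers, multiplied by the ratio.

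| f | m | s | z ratio | Relative efficiency | Power if 80% in daily smokers |
|---|---|---|---|---|---|
| 20% | 1.5 | 1.3 | √(1.69/2.14) = 0.89 | 0.79 | 70% |
| 30% | 2.0 | 1.4 | √(1.96/3.16) = 0.79 | 0.62 | 60% |
| 40% | 2.5 | 1.5 | √(2.25/4.75) = 0.69 | 0.47 | 49% |

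**4. Effect of adjusting for baseline daily/occasional status.** Adjustment removes the mixture term f(1 − f)·m² and leaves residual variance (1 − f)·s². With n per arm:

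z = (1 − f)·d / √[2(1 − f)·s²/n] = d·√[(1 − f)·n/2] / s.

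This is exactly the z from daily smokers alone. Under the floor model, the whole power loss in step 3 is therefore due to not adjusting.

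**5. Second set of assumptions, including a smaller share.** Effective n per arm 455/1.12 = 406.25; daily smokers with mean 2, SD 1.5 and effect 0.3 points (0.2 SD).

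| f | Arm difference, all | Power, all, unadjusted | Power, all, adjusted for status | Power, daily smokers only |
|---|---|---|---|---|
| 0% | 0.30 | 81% | 81% | 81% |
| 10% | 0.27 | 70% | 77% | 77% |
| 20% | 0.24 | 59% | 72% | 72% |
| 30% | 0.21 | 49% | 67% | 67% |
| 40% | 0.18 | 39% | 60% | 60% |

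The last two columns agree, as step 4 requires. They still fall as f rises, because fewer participants carry the effect. Adjustment does not recover that part, and neither does restriction to daily smokers.

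**The case against.** **The floor is not shown in the document.** A reader might infer that the index cannot register any change in occasional smokers. The article does not support that. It gives no score categories, so a complete floor cannot be demonstrated from it. Time to first cigarette is asked of all participants and can vary on smoking days. An occasional smoker who takes up daily smoking moves up the index, so prevented escalation is detectable. Not every occasional smoker is at the eligibility minimum either. All of this stands, and it limits the point to little room for reductions.

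**Dependence is not consumption.** A low score in a light smoker may correctly describe low dependence. This also stands: the index is not wrong as a dependence measure. But it leaves the coached fall in weekly cigarettes without a suitable outcome.

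**The smaller mean difference is not bias.** If occasional smokers move little on the index, (1 − f)·d, which is 60% to 80% of the daily smokers' difference at the assumed shares, is the average effect in the randomised sample. That is a matter of estimand. It gives no reason to drop randomised participants, and step 4 shows that dropping them gains no power over adjustment.

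**Model detail belongs in a full protocol or SAP.** Scoring rules and model form may well be there, and their absence here is not criticised. The article does, however, fix the instrument and its two items, and it states a rule for covariates under which they enter only in response to baseline differences. That rule does not secure the adjustment, because the precision gain comes from the covariate's link with the outcome, whether or not the arms differ at baseline.

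**Conclusion.** The point holds in a limited form. The index rests on two per-day items in a sample whose occasional smokers the article itself counts per week, so it has little room to show a reduction in them. An unadjusted all-participant comparison is likely to lose precision from the daily/occasional mixture.

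The size is unknown. The range of 70% down to 49% power, against 80% in daily smokers, rests on assumed shares of 20% to 40%, assumed index means and SDs, and occasional smokers fixed at the bottom score. Smaller shares or a softer floor would reduce the loss. Adjustment for baseline smoking status recovers it in full under the same model.

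A reader might also infer that the trial is underpowered or that occasional smokers should be left out of the index comparison. Neither follows. One secondary outcome is affected, the primary outcome and N = 910 are untouched, and exclusion would change the population described without a gain in power over adjustment.

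**What to change.** In Outcomes and Data analyses:

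1. Keep all participants in the index comparison, and always adjust for baseline daily/occasional status and the baseline index, whether or not the arms differ at baseline. Smoking status and both index items are collected before allocation is released, so the intervention cannot affect them.
2. Report the index in baseline daily smokers as a supportive analysis.
3. Add cigarettes per week at follow-up in all participants, with daily counts multiplied by 7, adjusted for the baseline count, as the measure of the coached reduction.

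Settle this before outcome data are seen, so that neither the covariates nor the subset look chosen by the results. The cost is one more secondary comparison and a per-week answer option for occasional smokers in the follow-up interview. The baseline data are already planned, and the index already requires a consumption question at follow-up.

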### Data analyses

We will use regression models to test the efficacy of the intervention on the different outcome measures. If necessary, we will control for baseline differences by adding additional baseline variables as covariates to the regression models. All analyses will be performed considering the intention-to-treat principle. Given the clustered nature of the data (apprentices within school classes) we will compute robust variance estimators for all regression analyses.

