### Randomisation and allocation concealment

To avoid spill-over effects within school classes, we will conduct a cluster-randomised controlled trial using school class as a randomisation unit. Due to the heterogeneity of apprentices in the different vocational schools (e.g. concerning gender or professions), we will use separate randomisation lists for each vocational school (stratified randomisation). Furthermore, to approximate equality of sample sizes in the study groups, we will use block randomisation with computer generated randomly permuted blocks of 4 cases [18].

The study assistants supervising the baseline assessment in the vocational schools will be blinded concerning group allocation of the school classes. Also, group allocation will not be released to study participants until having provided informed consent, their username, mobile phone number, and baseline data of the above mentioned smoking-related variables. Furthermore, the study assistants conducting the computer assisted telephone interviews at follow-up will be blinded when assessing the primary and secondary outcome measures.

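### Covariate adjustment of the primary model depends on observed baseline differences instead of being fixed in advance

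*Protocol article*

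**What the plan says.** The Data analyses section begins: "We will use regression models to test the efficacy of the intervention on the different outcome measures". The next sentence gives the covariate rule: "If necessary, we will control for baseline differences by adding additional baseline variables as covariates to the regression models". It applies to every outcome model, including the one for the primary outcome, 7-day point prevalence abstinence at six months. For clustering by class the section adds: "we will compute robust variance estimators for all regression analyses".

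Two other sections bear on the rule. Under Participant recruitment and baseline assessment, all participants supply "intention to quit, daily/weekly cigarette consumption, time to first cigarette in the morning, past quit attempts, smoking status of friends and parents", together with age of smoking onset; demographic data come from the screening. Under Randomisation and allocation concealment, classes are randomised from a separate list for each vocational school. Participants learn their allocation only after they have given the smoking-related baseline data.

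The Sample size calculation rests on an unadjusted chi-square test.

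**The concern.** Under random allocation of classes, baseline differences between arms are mainly chance. Whether the arms happen to differ on a variable says little about whether adjusting for it is worthwhile; that depends on how well the variable predicts abstinence. A rule that waits for imbalance therefore leaves predictive variables out of the model in most realisations of the trial, and their precision is lost.

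The rule also leaves the form of the primary analysis to a judgement made after the baseline data are seen. If the model is logistic, that judgement affects more than precision. The planned 25% versus 17% is a marginal odds ratio of (0.25 × 0.83)/(0.75 × 0.17) = 1.63. Conditioning on prognostic covariates gives a different, conditional odds ratio, so chance imbalance would partly decide which quantity is reported.

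At stake are some power and a primary result that is not fixed before the comparison is made. The validity of the trial is not at stake.

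**Working it through.** **1. The plan's own figure.** Inputs from Sample size calculation: 25% versus 17%, two-sided 5%, 80% power, cluster size 7, intra-cluster correlation 0.02.

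n = [1.960 × √(2 × 0.21 × 0.79) + 0.842 × √(0.25 × 0.75 + 0.17 × 0.83)]² / 0.08² = 405.7, so 406 per group. The design effect is 1 + (7 − 1) × 0.02 = 1.12, and 406 × 1.12 = 454.7, so 455. Both figures reproduce. Power at 455/1.12 = 406.25 effective participants per group is 80.0%.

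**2. Power with fixed adjustment.** If the covariates explain a share R² of outcome variance, the effective size is approximately 406.25/(1 − R²). The article gives no R², so the range is an assumption.

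| Assumed R² | Power at 455 per group | n per group equivalent to 455 unadjusted |
|---|---|---|
| 0 | 80.0% | 455 |
| 0.02 | 80.8% | 446 |
| 0.05 | 82.0% | 432 |
| 0.10 | 84.0% | 410 |
| 0.15 | 86.0% | 387 |
| 0.20 | 88.0% | 364 |

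**3. How often chance would trigger adjustment.** Suppose that adjustment is deemed necessary when a baseline test gives p < 0.05 (an assumption; the article names no criterion). With 7 independent covariates, at least one triggers in 1 − 0.95⁷ = 30% of trials. With 5 covariates it is 23%, and with 10 it is 40%.

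**4. Simulation of the rules.** Set-up: 130 classes of 7 (910 participants), 7 hypothetical covariates, logistic regression with class-robust standard errors and 4,000 runs per setting. *Triggered* adjusts only for covariates with a significant baseline difference. *Best of three* takes the smallest p-value among the unadjusted, fully adjusted and triggered models.

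Rejection rate with no effect (%):

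| R² | Unadjusted | Always adjusted | Triggered | Best of three |
|---|---|---|---|---|
| 0.028 | 5.55 | 5.50 | 5.65 | 6.58 |
| 0.061 | 4.75 | 5.08 | 4.62 | 6.48 |
| 0.100 | 5.32 | 5.38 | 4.95 | 7.45 |

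Power at 25% versus 17% (%):

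| R² | Unadjusted | Always adjusted | Triggered | Loss, triggered against always |
|---|---|---|---|---|
| 0.031 | 81.62 | 82.42 | 81.50 | 0.92 |
| 0.066 | 82.25 | 85.05 | 82.80 | 2.25 |
| 0.115 | 80.95 | 86.45 | 81.42 | 5.03 |

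The Monte Carlo standard error is √(0.05 × 0.95/4000) = 0.3 points in the first table and about √(0.8 × 0.2/4000) = 0.6 points in the second. All rules were fitted to the same simulated data, so the comparisons are paired. Unadjusted power lies slightly above the planned 80%, so the differences between rules matter more than the levels. School strata were not simulated.

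A simpler simulation with 2 × 406 = 812 independent participants and six covariates gave 5.9%, 6.0% and 7.8% for choosing the smallest p-value at R² of 0.05, 0.10 and 0.20. The two simulations together give the range of about 6 to 8%.

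**The case against.** The strongest reply is that a condensed article may leave the threshold, the covariate list and the choice of primary model to a fuller document. That is fair, and their absence is not the point here. What the article does fix is the direction of the rule: covariates enter in response to baseline differences. An analysis plan that only defined the threshold would keep the wrong trigger.

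It can also be said that adjusting for imbalance guards against selective consent within classes. Fixed adjustment for the same variables does this too, without waiting for a difference to appear.

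Four stronger readings are tempting, and the article supports none of them:

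- *The rule itself inflates the type I error.* The stated trigger is baseline differences, not outcome results, and the mechanical version stayed near nominal (4.6 to 5.7%, against 4.8 to 5.6% unadjusted). The 6 to 8% needs an analyst who picks the most favourable model, which the text does not describe. It only leaves room for it.
- *The choice will be made with outcomes in view.* The article does not say when it is made. Baseline data exist six months before the outcomes.
- *The trial is underpowered.* The sample size assumes no adjustment and reproduces exactly. What is forgone is power above the plan.
- *Strong predictors are being ignored.* The article lists the variables and says nothing of their prognostic strength.

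The odds-ratio argument is conditional as well: the article says only regression, without naming logistic.

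**Conclusion.** The point holds as a modest weakness in the primary analysis. Conditioning adjustment on observed imbalance is the wrong criterion, and it leaves the primary result (and, under a logistic model, the quantity estimated) to a judgement that could be settled beforehand.

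The triggered rule recovered little or none of the gain from always adjusting: its power stayed within about 0.6 points of the unadjusted analysis in every simulated setting. The absolute loss is small when the covariates are weak. All power figures rest on assumed R² values, and those for the triggered rule also assume a p < 0.05 trigger and 7 independent covariates. Neither the sample size nor the nominal error rate of a mechanically applied rule is at fault.

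**What to change.** Replace the conditional sentence with a primary model that adjusts, whatever the baseline comparison shows, for a short named set. An example is intention to quit, cigarette consumption, time to first cigarette, past quit attempts, age and sex. This assumes that age and sex are among the demographic data, which the article does not itemise.

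- Put consumption on one common scale first, because it is recorded per day or per week.
- Account for vocational school, the stratification factor, and keep robust variance by class.
- Report a marginal risk difference, which matches the scale of the sample size target, and give the unadjusted model as a sensitivity analysis.
- Adjust the nicotine dependence outcome for its own baseline value. Its two components, time to first cigarette and consumption, are collected at baseline.

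The cost is a short paragraph and slightly more analysis work, with no new data, recruitment or change of design. Sparse schools need care: 910/7 = 130 classes over about 30 invited schools is roughly 4 classes each if all take part, and some will have fewer. A rule for pooling small schools should be fixed at the same time.
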